# Investigation of frailty markers including a novel biomarker panel in emergency laparotomy: protocol of a prospective cohort study

**DOI:** 10.1186/s12893-023-02093-5

**Published:** 2023-07-05

**Keywords:** Emergency laparotomy, Frailty biomarkers, Mass spectrometry, Clinical Frailty Scale, Sarcopenia

## Abstract

**Background:**

Emergency laparotomy (EmLAP) is one of the commonest emergency operations performed in the United Kingdom (approximately 30, 000 laparotomies annually). These potentially high-risk procedures can be life changing with frail patients and/ or older adults (≥ 65 years) having the poorest outcomes, including mortality. There is no gold standard of frailty assessment and no clinical chemical biomarkers existing in practice. Early detection of subclinical changes or deficits at the molecular level are essential in improving our understanding of the biology of frailty and ultimately improving patient outcomes. This study aims primarily to compare preoperative frailty markers, including a blood-based biomarker panel, in their ability to predict 30 and 90-day mortality post-EmLAP. The secondary aim is to analyse the influence of perioperative frailty on morbidity and quality of life post-EmLAP.

**Methods:**

A prospective single centred observational study will be conducted on 150 patients ≥ 40 years of age that undergo EmLAP. Patients will be included according to the established NELA (National Emergency Laparotomy Audit) criteria. The variables collected include demographics, co-morbidities, polypharmacy, place of residence, indication and type of surgery (as per NELA criteria) and prognostic NELA score. Frailty will be assessed using: a blood sample for ultra-high performance liquid chromatography mass spectrometry analysis; preoperative CT abdomen pelvis (sarcopenia) and Rockwood Clinical Frailty Scale (CFS). Patients will be followed up for 90 days. Variables collected include blood samples (at post operative day 1, 7, 30 and 90), place of residence on discharge, morbidity, mortality and quality of life (EQ-5D-5 L). The frailty markers will be compared between groups of frail (CFS ≥ 4) and non-frail using statistical methods such as regression model and adjusted for appropriate confounding factors.

**Discussion:**

This study hypothesises that frailty level changes following EmLAP in frail and non- frail patients, irrespective of age. We propose that non- frail patients will have better survival rates and report better quality of life compared to the frail. By studying the changes in metabolites/ biomarkers in these patients and correlate them to frailty status pre-surgery, this highly novel approach will develop new knowledge of frailty and define a new area of clinical biomolecular research.

**Trial registration:**

ClinicalTrials.gov: NCT05416047. Registered on 13/06/2022 (retrospectively registered).

**Supplementary Information:**

The online version contains supplementary material available at 10.1186/s12893-023-02093-5.

## Background

Emergency laparotomy (EmLAP) is one of the commonest emergency operations performed in the United Kingdom with approximately 30,000 laparotomies performed annually in England and Wales [1]. Frail patients have been shown to have significantly poorer outcomes, especially in older adults (≥ 65 years) [2, 3]. According to the recent 8th patient report of National Emergency Laparotomy Audit (NELA), more than 22,000 patients underwent emergency laparotomy in a year and more than half (55.3%) of these patients were ≥ 65 years. The report found that risk of mortality doubled among frail patients undergoing EmLAP [4]. These findings were mirrored in the first multi-centred observational study, the Emergency Laparotomy Study (ELF study) [5]. Using the Rockwood Clinical Frailty Scale (CFS), the ELF study reported 20% of older adults had frailty pre-EmLAP. As frailty increased, independent of age, 30-day 90-day morality did too. Furthermore, the presence of frailty resulted in an increased level of dependence at discharge highlighting the significant and prolonged health demands of frailty.

Frailty is a clinical syndrome of increased vulnerability that results from ageing associated multi-system physiological decline [6]. Such a decline reduces the ability of the individual to cope with physiological stress such as surgery (surgical frailty) and negatively impact on their quality of life. Frailty can be identified using different questionnaires and assessments depending on what aspect of the syndrome is being looked at. This includes but not limited to muscle wasting (sarcopenia), malnutrition, cognition (memory, orientation and processing), physical function and capacity [7–10]. Most studies associate frailty with the older population, but frailty has also been shown to exist in younger individuals [11]. Moreover, there could be a time gap between biological changes and phenotypic manifestations of frailty (pre- frail) [12]. To date, there isn’t a frailty assessment tool that has been identified as the gold standard for assessing frailty in all clinical situations including emergency setting. Hence, an objective measurement of frailty is required to not only identify and modify frailty, but in understanding the biology of ageing that leads to a clinical diagnosis of frailty.

One of the largest research studies on role of metabolomics in frailty [13] demonstrated how mass spectrometry can be used to understand changes in blood metabolism across frailty. Serum samples from 1200 people from within the English Longitudinal Study of Ageing (ELSA- www.elsa-project.ac.uk) were chemically profiled and mapped on to associated Rockwood Frailty Index calculations and altered levels of 12 metabolites were found to be dysregulated in those that were consider frail. These included 3 tocotrienols and 6 carnitines- metabolites known to be directly involved in energy metabolism, which was used to differentiate between frail and non-frail patients. These findings indicated that decreased energy production acts as a common pathway and a primary driver toward frailty which was reflected globally by frail individuals presenting symptoms of weakness, slowness, exhaustion and low activity. These results provided a platform for this study to establish a panel of novel frailty biomarkers in emergency laparotomy patients and correlate blood metabolites with changes in frailty due to EmLAP, postoperative morbidity and mortality.

No clinical chemical biomarkers for frailty currently exist in practice due to a lacking in the understanding of the biochemical aetiology of frailty. However, early detection of subclinical changes or deficits at the molecular level are essential in improving our understanding of the biology of frailty and ultimately improving patient outcomes, aiding in shared decision-making, precision medicine and development of new optimal postoperative EmLAP patient pathway.

The primary aim of this study is to compare preoperative frailty markers including establishing a novel blood-based biomarker panel that could identify frailty in EmLAP patients and their ability to predict 30 and 90-day mortality post-EmLAP. The secondary aim is to analyse the influence of perioperative frailty on 30-day morbidity and quality of life post-EmLAP.

## Methods/ designs

### Patient recruitment

A prospective single centred observational study will be conducted in a National Health Service hospital that has an acute emergency surgical service. All consecutive emergency laparotomy (EmLAP) patients ≥ 40 years of age that undergo EmLAP will be screened and recruited. For patients who were deemed to have a lack of capacity to consent, their next of kin or welfare attorney will be approached to obtain written consent for the study pre-operatively. When the participant regains capacity, they will be approached to re-obtain consent to continue participation. Patients who do not regain capacity, the consent from next of kin or welfare attorney will continue. All recruited patients will be followed up for 90 days. The data collected after gaining consent and up to 90 days follow up are summarised in Fig. 1. Participant’s details will be pseudo-anonymised with a study ID.

### Inclusion criteria

Age ≥ 40 years.English and non- English speaker (usage of language line to obtain consent).NELA inclusion criteria [4].

### Exclusion criteria

Under 40 years of age.CT scan or postoperative finding of inoperable disseminated peritoneal disease.Open and close laparotomy (postoperative palliation, non-survivable global ischemia where there are < 90 cm from duodenojejunal junction to stoma).Complication from colonic stenting requiring laparotomy.NELA exclusion criteria [4].

### Data collection

The majority of data will be obtained from the routine admission documentations and electronic patient record and recorded in an online password protected spreadsheet. The variables recorded will include:

1) Demographics: Age, gender, deprivation score/ Scottish Index Multiple Deprivation (SIMD) [14] score (1 to 5), ethnic origin.

2) Co-morbidities: Charlson co- morbidity index (number of co-morbidities < 5 or ≥ 5) [15].

3) Polypharmacy (> 5 regular medications).

4) Lifestyle: alcohol intake (unit per week), smoking status (currently, ex-smoker < 5 year, ex-smoker ≥ 5 years, never smoked), weight and Body Mass Index.

5) Place of residence: home and independent, home with carers, home with family support, sheltered housing, nursing home.

6) Indication for and type of surgery: as per NELA criteria [4].

7) Prognostic scores: NELA score.

8) ASA (American Society of Anaesthesiology) score [16].

Frailty markers (pre-operative):

1) Plasma samples obtained using 6ml lithium heparin tubes for ultra-high performance liquid chromatography mass spectrometry analysis (UHPLC-MS).

2) Sarcopenia on CT abdomen pelvis [17].

3) Malnutrition Universal Screening Tool (MUST) score.

4) Routine Abbreviated Mental Test (AMT) score.

5) Routine serum biochemistry and haematology: Hb, White cells, neutrophils, C- Reactive protein, Albumin.

6) Rockwood Clinical Frailty Scale (CFS; assessing the baseline frailty status 2 weeks before admission with scores from 1 to 9 as frailty increases). Score of ≥ 4 will be grouped as frail [8].

Follow up variables recorded are:

1) Day 1, day 7 or discharge day if before day 7, day 30 and day 90 blood samples.

2) Total hospital stay including critical care stay.

3) Place of residence post discharge following emergency laparotomy.

4) Day 30 readmission.

5) Day 30 morbidity/ complications (according Clavien-Dindo classification Surgical Complications) [18].

6) Day 30 and day 90 mortality.

7) EQ-5D-5L on day 30 and 90.

8) Day 90 CFS.

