### Ultra-high Performance Liquid Chromatography mass spectrometry analysis

A semi-targeted ultra-high performance liquid chromatography mass spectrometry-based metabolomics approach (UHPLC-MS) will be performed to determine metabolic signatures correlated to frailty status and surgical outcome. This will be performed on a Thermo Exploris 240 mass spectrometer coupled to a Thermo Vanquish binary liquid chromatography instrument. The applied method will contain a range of predefined targeted mass measurements (using product ion multiple reaction monitoring) related to a defined group of biochemically annotated metabolites already identified in previous research [13] which include 13-carboxy-alpha-tocotrienol, stearoylcarnitine, vaccenyl carnitine, urocortisol, 13-carboxy gamma-tocotrienol, hexacosonyl carnitine, formyl-N-acetyl-5-methoxykynurenamine, arginine, gamma-tocotrienol, linoleyl carnitine, arachidonic acid and prostaglandin G2. A range of other chemical classes will also be targeted that will cover aspects of dietary response and polypharmacy – determined by pre-operative information provided by the patient cohort.

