### Statistical analysis

The categorical variables (demographics, co-morbidities, polypharmacy, ASA score) will be expressed as n and percentage (%) and continuous variables (age) as mean ± standard deviation. The frailty markers (score 1–9) will be compared between groups of frail (CFS ≥ 4) and non-frail (CFS ≤ 3). Categorical variables will be analysed using Chi-square or Fisher Exact test. All normally distributed continuous variables will be assessed with Student’s T-test or the ANOVA test and for the non- normal distribution variables, the rank based Kruskal- Wallis non-parametric test will be used to determine the statistical significance between the different groups.

The primary analysis of metabolomics data will involve a range of pre-processing normalisation procedures to help scale the differences in the magnitude of metabolite concentrations. Normalised features will then be compared for analytical reproducibility by using multivariate principal component analysis (PCA) to determine QC clustering and outlier identification. Further analysis of clinical frailty markers and between groups of frail and non-frail (defined by clinical frailty scale binning) using the Kruskal-Wallis t-test or Mann Whitney test and subsequently in a regression model and propensity score matching, adjusting for appropriate demographics and other baseline variables. A linear mixed model will also be used on the normalised data to study the changes of each metabolite over time to identify differences between frailty status, response post-surgery and polypharmacy interactions.

The association between frailty markers and mortality will be analysed using regression model and will be adjusted for confounding factors such as presence of sepsis and type of surgery. Sensitivity and specificity analyses will be performed using the Receiver Operating Characteristic curve (ROC). A p-value of < 0.05 is considered statistically significant.

Result from EQ-5D-5L questionnaire will be reported and analysed quantitatively (means and ranges of 5 domains) using the analysis tool (index value set calculator and analysis of observational descriptive systems data) provided by the EuroQol Office [22].

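### Keep the medication count behind the more-than-5 flag and record feeding state at each blood draw, so that the metabolite models can use both

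*Protocol article*

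**What the plan says.** Three sections of the protocol article bear on this.

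- **Data collection.** The baseline list opens with "The variables recorded will include" and gives medication as one item, "Polypharmacy (> 5 regular medications". The nearest items to diet are alcohol units, weight, BMI and the MUST score. The source is described thus: "The majority of data will be obtained from the routine admission documentations and electronic patient record". The follow-up list has eight items, among them the day 1, 7, 30 and 90 blood samples. None is feeding or fasting status.
- **Mass spectrometry section.** Besides the twelve named metabolites, the assay is to "cover aspects of dietary response and polypharmacy – determined by pre-operative information provided by the patient cohort".
- **Statistical analysis.** Polypharmacy is summarised as a categorical variable. A linear mixed model then follows each normalised metabolite over time "to identify differences between frailty status, response post-surgery and polypharmacy interactions".

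**The concern.** The assay and the model ask more of the medication and diet data than the listed variables provide. A yes/no at more than 5 medicines gives the same value to a patient on 6 and a patient on 15, and it does not say which drugs they are. Feeding state at the draws is not listed at all.

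The named targets include carnitines, arachidonic acid and arginine, which plausibly respond to feeding. Intake is likely to change sharply between the preoperative, day 1, day 7 and later samples, and frail patients may eat less and take more medicines than others. If so, part of a frail versus non-frail difference in metabolite trajectory could be a feeding or drug effect. The Background reads altered levels of these metabolites as reduced energy production in frailty, and the Discussion intends to map metabolite changes through surgery on to biochemical pathways. That reading is what is at stake. The mortality comparison is affected much less.

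**Working it through.** The plan gives no figure to reproduce on this point. The check has three steps.

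**1. What the listed variables support.**

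| Planned use | Needs | Listed |
|---|---|---|
| Polypharmacy-by-time or polypharmacy-by-frailty term | Any polypharmacy variable | Yes, the flag |
| Drug-class effects; choice of drug-related targets | Drug names | Not listed; the assay section refers to preoperative patient information without naming the items |
| Separating feeding from frailty over time | Feeding state at each draw | Not listed |

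**2. What the flag discards.** Let X be the number of regular medicines, with mean m and SD s, and let the flag be 1 when X > 5, with probability q. Let d be the difference in mean count between flag = 1 and flag = 0. The share of the variance of X that the flag keeps is

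r² = q(1 − q)d² / s².

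The documents give no count distribution. The values of m and s below, and the negative binomial form, are assumptions.

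| m, s | q | Mean count if > 5 | Mean count if ≤ 5 | d | r² | Lost |
|---|---|---|---|---|---|---|
| 4, 3 | 0.258 | 8.09 | 2.58 | 5.50 | 0.64 | 36% |
| 5, 3.5 | 0.372 | 8.64 | 2.84 | 5.79 | 0.64 | 36% |
| 6, 4 | 0.478 | 9.25 | 3.03 | 6.22 | 0.60 | 40% |

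First row: 0.258 × 0.742 × 5.50² / 9 = 0.64. Other pairs with m from 4 to 6 and s from 3 to 4 give r² from 0.61 to 0.65. The flag therefore loses about 35% to 40% of the variance in the count.

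**3. What an unrecorded feeding state does.** Take one metabolite and one feeding state, for example nil by mouth, that shifts it by g. Let b(t) be the frail minus non-frail difference at draw t with feeding held equal. Let p₁(t) and p₀(t) be the proportions of frail and non-frail patients in that state. A model without feeding estimates

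b(t) + g[p₁(t) − p₀(t)].

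The estimated change from the preoperative draw (t = 0) is

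b(t) − b(0) + g{[p₁(t) − p₀(t)] − [p₁(0) − p₀(0)]}.

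Every 10 percentage points by which the gap between the groups changes add 0.1g to the frailty-by-time estimate. If feeding follows the same pattern in both groups the term is zero. Neither g nor the proportions are in the documents, so no size can be given. Without a feeding record the term can be neither estimated nor removed.

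**The case against.** The best reply is that this is a condensed article. The baseline list is open-ended, the figure summarising data collection is not shown, and a full protocol exists. The assay section itself says that its drug and diet targets are "determined by pre-operative information provided by the patient cohort", so such information is evidently obtained. The flag also cannot be set without counting medicines. This largely stands for drug names and diet history: their absence from the list does not show that they are not collected.

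A reader might go further and infer that the planned polypharmacy interactions cannot be produced. The documents do not support that. The analysis section does not say that it means specific drugs, and a binary variable is enough for an interaction term.

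A reader might also take the 35% to 40% as the share of confounding that remains. It is not. It is variance lost from the count under assumed distributions. Reading it as residual confounding would also require the metabolite effect and the link with frailty to be linear in the count.

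It can further be said that diet- and drug-related compounds measured in the plasma carry some exposure information, and that MUST, albumin and BMI give nutritional context. Both are true, so it would be wrong to call the information nil. But the plan does not say that measured compounds will serve as covariates, and none of these items records how a patient was being fed when a sample was drawn.

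The reply is weakest for feeding after surgery. The follow-up list is worded as a complete list, unlike the baseline one, and feeding is not in it.

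**Conclusion.** The point holds as an improvement to the metabolite models, not as a contradiction that blocks them. The flag supports an interaction term but loses about 35% to 40% of the variance in the count; this rests on negative binomial counts with mean 4 to 6 and SD 3 to 4. The feeding gap is the more important part. On the variables listed, feeding effects cannot be separated from frailty-by-time differences. How much that matters depends on two things the documents do not give: how strongly each metabolite responds to feeding, and how differently frail and non-frail patients are fed at each draw. The study is exploratory, so the change is desirable rather than essential.

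**What to change.** 1. Keep each patient's regular-medicine list from the electronic record, which gives count and class. Use the count in place of the flag in the mixed model, and keep more than 5 for description.
2. At each of the five samples record one feeding code: nil by mouth, oral/enteral, or parenteral. Report the mixed model with and without this code as a time-varying covariate. Both are needed: feeding after surgery may lie partly on the path from frailty to metabolite change, and adjusting for it would then remove part of the effect of interest.
3. State whether polypharmacy interactions means the medication count or drug classes, and name the preoperative items from which the drug- and diet-related targets are chosen.

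The cost is a few extra data fields and one or two more model terms. The medicine list, and probably the feeding code, could be recovered from routine records for patients already enrolled, although the documents do not confirm that these records hold feeding state.

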**Fig. 1 Fig1:**
[figure not shown]
The data collected after obtaining consent including follow up period. MUST: Malnutrition Universal Screening Tool; AMT: Abbreviated Mental Test; CFS: Rockwood Clinical Frailty Score

### Assessment of Sarcopenia

Participants of this study who underwent CT abdomen pelvis pre- operatively will be measured for sarcopenia [17]. The measurement of total cross-sectional area of psoas muscle (total psoas area, TPA) on L3 vertebra level will be performed using PACS (Picture Archiving and Communication System software). The area measured is standardised by measuring at the level where both L3 transverse processes were maximally in view on CT. The TPA is standardised for patient height using formula of TPA (mm^2^)/ height (m^2^) providing the total psoas index (TPI). The TPI will be stratified according to gender with sarcopenia being present in the lowest quartile [19].

Calculations of inter and intra- class correlation coefficients (ICCC) will be performed to ensure reliability of the measurement technique. The inter and intra ICCC will be calculated where the r^2^ value of > 0.8 indicates excellent correlation and ICCC value close to 1 indicates high similarity and high reliability.

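### Sarcopenia is defined as a yes/no lowest-quartile class of a continuous psoas index; used in that form, the CT marker gives up nearly half its information in the mortality comparison

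*Protocol article*

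**What the plan says.** Under Assessment of Sarcopenia, the Protocol article says who is measured: "Participants of this study who underwent CT abdomen pelvis pre- operatively will be measured for sarcopenia [17". Psoas area at L3 is divided by height squared, "providing the total psoas index (TPI", which is a continuous quantity. The next step makes it a category: "The TPI will be stratified according to gender with sarcopenia being present in the lowest quartile [19". The section gives no threshold in mm²/m² and names no reference distribution; it only cites reference 19.

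Under Data collection, the CT entry among the preoperative frailty markers reads "Sarcopenia on CT abdomen pelvis [17". TPI is not listed there. The Clinical Frailty Scale (CFS) is recorded from 1 to 9 and is also grouped: "Score of ≥ 4 will be grouped as frail [8".

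The abstract states the primary aim as to "compare preoperative frailty markers, including a blood-based biomarker panel, in their ability to predict 30 and 90-day mortality", and the Background section repeats it. Under Statistical analysis, the association of the markers with mortality is to be examined by adjusted regression, and "Sensitivity and specificity analyses will be performed using the Receiver Operating Characteristic curve (ROC". That section does not say in which form the CT marker enters.

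**The concern.** The study exists to rank markers against each other. A marker cut to yes/no before the ranking is judged partly on the cut. Its ROC curve is two straight segments through a single point, while a continuous metabolite keeps its whole curve. If sarcopenia then shows a lower AUC or a weaker association with death, a reader cannot tell whether muscle mass predicts poorly or the quartile rule discarded the signal.

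The rule itself raises a second question. A quartile is relative to some distribution. If that distribution is this cohort, the share called sarcopenic is 25% of each sex however wasted or well-muscled the patients are. The reported prevalence then carries no information, and the cut-off is an estimate from a modest sample.

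**Working it through.** The plan states no sarcopenia prevalence, TPI cut-off or expected marker accuracy, so there is no figure of its own to reproduce on this point.

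**Inputs from the Protocol article:** lowest quartile within gender; target of 150 patients; 20% anticipated dropout, hence 150 × 0.80 = 120; significance at p < 0.05.

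**Assumptions, not in the document:** TPI normal within sex; mortality 8-20%; continuous AUC 0.65-0.75; 60-75 patients with a CT per sex (120/2 to 150/2, that is, an equal sex split and a CT in everyone analysed); two-sided test.

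**1. Information kept by the cut.** For a normal marker split at quantile p, the share kept is φ(z_p)² / [p(1−p)]. With p = 0.25, φ(z_p) = 0.3178, so 0.3178² / 0.1875 = 0.539. The loss is 1 − 0.539 = 46%. In these terms 150 patients carry the information of about 150 × 0.539 = 81, and 120 that of about 65. In a logistic model simulated with 200,000 subjects and mortality of 12-15%, the yes/no version kept 61-64% of the likelihood-ratio chi-square, a loss of 36-39%.

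**2. AUC after the cut.** In an equal-variance binormal model the separation is d = √2 × Φ⁻¹(AUC). The cut c is solved so that overall positivity is 25%: m·Φ(c+d) + (1−m)·Φ(c) = 0.25, where m is mortality. The AUC of the yes/no marker is (sensitivity + specificity)/2.

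Example with AUC 0.70 and m = 10%: d = 0.742 and c = −0.762. Sensitivity is Φ(−0.020) = 0.492 and specificity is 1 − Φ(−0.762) = 0.777, so the AUC is (0.492 + 0.777)/2 = 0.634.

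| Continuous AUC | Yes/no AUC, m = 8% | m = 10% | m = 15% | m = 20% |
|---|---|---|---|---|
| 0.65 | 0.597 | 0.597 | 0.595 | 0.594 |
| 0.70 | 0.635 | 0.634 | 0.632 | 0.630 |
| 0.75 | 0.676 | 0.675 | 0.672 | 0.668 |

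Between 63% and 70% of the excess over 0.5 is kept, so 30-37% is lost.

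**3. Power.** With 120 patients, 15% mortality and continuous AUC 0.70, power to detect an association with death is 83% for the continuous marker and 65% for the class.

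**4. If the quartile is the cohort's own.** In simulation with 60 per sex, prevalence stayed at 25% when mean TPI was shifted by 0, −0.5 or −1 SD. A fixed external cut gave 25%, 43% and 63%. The standard error of the sample quartile is √(0.25 × 0.75/n)/φ(z_0.25): √(0.1875/60)/0.3178 = 0.176 SD for n = 60, and √(0.1875/75)/0.3178 = 0.157 SD for n = 75. With 60 per sex, the estimated cut falls between about the 16th and 37th population percentile in 95% of samples.

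**The case against.** The strongest reply is that the article defines a diagnostic category and does not say that only this category enters the models. Statistical analysis leaves the form of every marker open, TPI is available as a number, and variable coding is commonly left to an analysis plan. This stands in part. The loss arises only if the class is the analysis variable, and the document does not settle that. But the text is not merely silent: it chooses a relative, two-level definition and lists sarcopenia, not TPI, as the marker to be compared.

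Four stronger readings are tempting, and the document does not support them:

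- A reader might infer that the cut removes most of the marker's information. It does not: about 54% is kept under a normal model, and 61-64% on the logistic scale.
- A reader might take it as stated that the quartile is this cohort's. That is the natural reading, since TPI is measured in the participants and no other distribution is named. But reference 19 is not at hand and might supply an external cut. The fixed 25% prevalence and the sampling error of the cut would then fall away, while the loss from the split would remain.
- A reader might say the CT marker is handicapped against a nine-level CFS. The plan also groups CFS at 4 or above, so if stated groupings are the analysis variables, CFS is binary too. The secure contrast is with continuous markers such as the metabolites.
- A reader might say a sample quartile cannot be applied to a new patient. It yields a number for each sex that could be reported and applied. It would be imprecise, not unusable.

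The study also calls itself exploratory, which tempers the power figure. It does not remove a distortion in the comparison that is the primary aim.

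**Conclusion.** The point holds in limited form. If the CT marker enters as the class the article defines, it forfeits nearly half its information (46% under normality, 36-39% on the likelihood-ratio scale). Its AUC falls by about 0.05 to 0.08 when the continuous AUC is 0.65-0.75 and mortality 8-20%. A drop of that size could place it below a continuous marker of equal prognostic value. These sizes rest on a normal TPI and on assumed accuracy and mortality, none of which the document gives.

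The fixed 25% prevalence and the imprecise cut-off (standard error about 0.16-0.18 SD with 60-75 patients with CT per sex) are conditional on the quartile being the cohort's own. What is certain from the text is that neither the source nor the value of the cut-off is stated. This should be corrected before analysis. It does not threaten the conduct of the study.

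**What to change.** State under Statistical analysis that the CT marker in the mortality regression and all ROC comparisons is continuous TPI, either as a sex-specific z-score or as TPI with a sex term.

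Keep the lowest-quartile class as a secondary descriptive category. Under Assessment of Sarcopenia, state whether the quartile comes from this cohort or from reference 19, and give the numeric mm²/m² cut-off for each sex (or commit to reporting it, if it is estimated from the sample). If it is the cohort's own, label it a within-sample definition and do not present its 25% as a prevalence finding.

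The cost is a few sentences. TPI is already derived for every participant with a preoperative CT, so no new measurement or data collection is required.
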